### Procedures

#### Overview

The study plan is summarized in Table 2.

**Table 2 table2:** Study plan including the data and time points at which these are assessed.

Data	Day 0 (visit 1)	Month 3 (visit 2)	Month 6 (visit 3)	Month 12 (visit 4)	Month 24 (visit 5)
Consent	✓				
Inclusion or exclusion criteria	✓				
Randomization	✓				
AI^a^ system (intervention group)		✓	✓	✓	✓
Demography, transplant data, medical history, and height	✓	✓	✓	✓	✓
CollaboRATE score	✓	✓	✓	✓	✓
Control preferences scale	✓	✓	✓	✓	✓
Qualitative interviews	✓	✓	✓	✓	✓
Recall	✓	✓	✓	✓	✓
Vital signs (BP^b^, HR^c^, and weight)	✓	✓	✓	✓	✓
Safety lab	✓			✓	✓
Serum creatinine and eGFR^d^	✓	✓	✓	✓	✓
Proteinuria or albuminuria	✓	✓	✓	✓	✓
HLA^e^ antibodies	✓			✓	
Tacrolimus trough level	✓	✓	✓	✓	✓
Quality of life (PROMIS-29^f^)	✓	✓	✓	✓	✓
Clinical assessment	✓	✓	✓	✓	✓
AEs^g^ or SAEs^h^, AEs of interest, graft loss, and death	✓	✓	✓	✓	✓
Hospitalizations (reason, length, and type)	✓	✓	✓	✓	✓
Physician visits and contacts	✓	✓	✓	✓	✓
Immunosuppression	✓	✓	✓	✓	✓
Prior or concomitant medications	✓	✓	✓	✓	✓

^a^AI: artificial intelligence.

^b^BP: blood pressure.

^c^HR: heart rate.

^d^eGFR: estimated glomerular filtration rate.

^e^HLA: human leukocyte antigen.

^f^PROMIS-29: Patient Reported Outcomes Measurement Information System 29.

^g^AE: adverse event.

^h^SAE: serious adverse event.

#### Details of the AI-Based DSS and Recommended Procedures

An AI-based prediction model will be implemented to provide real-time predictions of the 1-year risk for graft loss based on the patient’s clinical, laboratory, immunological, and histopathological data. A previous version of the prediction model has been described in detail before, and all substantial changes will be made publically available. The predictions are provided as regression scores from 0 to 100 with higher scores indicating higher risk. For ease of interpretability, each score is classified into low-, medium-, or high-risk categories, which are color-coded as green, yellow, and red. Along with the risk score and risk category over time, relevant risk factors are provided to increase interpretability for the latest risk assessment.

Physicians will undergo training, in which technical details of the underlying model (training cohort, inclusion and exclusion criteria, end point definition, and performance), and results of preclinical studies are presented [11]. Hereby, the physicians can gain familiarity with the AI-DSS and also discuss potential limitations with the developers and study physicians. These training sessions will be recorded and analyzed as part of the qualitative subproject.

During the study, the physicians are advised to use the AI-DSS as an additional source of information and be especially cautious in case of high risks detected by the AI-DSS. In any case, it will be left to the physician’s choice on how to include the system’s information in the conversation with patients and support persons.

However, if the AI-DSS shows a high risk for graft loss, the physicians are free to discuss this with the patient and offer 1 procedure depending on their own assessment. First, physician—high risk for graft loss: if the physician agrees that there is a high risk of graft loss in a patient during the next year, the physician is advised to discuss this risk with the patient, when the situation is appropriate (enough time, no other major problems to be discussed, etc) or to discuss it during the next appointment. The physician should assess, whether the preferred renal replacement modality (hemodialysis, peritoneal dialysis, and retransplantation) of the patient is known and take measures to ensure a smooth transition without the need for emergency hospitalization (shunt planning, peritoneal dialysis catheter implantation, appointment for living donation, etc). Second, physician—low risk for graft loss: if the physician disagrees with the AI system and estimates a low risk for graft loss in a particular patient, the physician is advised to reconsider potential risk factors. The physician is free to incorporate or ignore the AI-DSS assessment into the SDM with patients and support persons.

#### Details on Qualitative Research Methodology

##### Overview

The physician-patient conversation will be recorded if physicians, patients, and support persons do not withdraw consent at randomization, as well as 3, 6, 12, and 24 months after randomization. Additionally, patients will be interviewed at randomization, as well as 3, 6, 12, and 24 months after randomization. Data collection at randomization, as well as 12 and 24 months after randomization will be conducted face-to-face, if possible and preferred by study participants. Data collection at 3 and 6 months after randomization will be conducted via telephone. This is to reduce the research-related burden on the participants. It has been suggested that telephone interviews produce similar quality data as face-to-face interviews [33-35]. Also, patients may appreciate being interviewed via telephone as they may feel more relaxed when being interviewed on the telephone and may find it easier to rearrange a telephone interview, rather than having to rearrange a face-to-face interview [36-39]. Participants will be encouraged to tell their views on how the AI-based DSS impacted physician-patient-support person communication and how treatment decisions were made, in the way they prefer, with as little interruption as possible from the interviewer. This narrative approach will help elicit the variety and interplay of potential factors related to treatment discussions [40]. The initial narrative will be followed by semistructured questions which will be developed based on a literature review and discussions among the research team which involves experts in the areas of medicine, communication and behavioral science, health services research, ethics, and medical informatics.

##### Influence of AI-Based Decision Support on the Normative Foundations of the Use of AI in SDM

Participants will be asked questions on their perceptions of concepts such as trust, agency, or transparency, for instance about how they evaluate the outputs of the tool and how these outputs relate to their physicians’ judgments. Participants may also be asked to report on their views on the system’s validity, effectiveness, and the perceived likelihood of errors, as well as on who is morally and legally liable for single treatment decisions.

##### Use of AI-Based Decision Support and Barriers and Enablers to its Implementation

Participants will be asked about their perceptions of acceptability, ease of use, agreement with specific components of the system’s outputs, and self-efficacy (ie, the belief that one can understand and use the system’s output). Participants will also be asked about further potential barriers to the use of AI in routine care, such as environmental factors like time pressure. These questions will be informed by the literature and discussions among the research team [41,42].

##### Sociodemographic and Disease Variables

Sociodemographic and disease variables obtained from patients and support persons will include gender, marital status, country of birth, postcode, highest level of education completed, income, and perceived health status. The support persons will also be asked to self-report their relationship to the patient and whether they are living with the patient. All sociodemographic and disease variables will be assessed at baseline and follow-ups to account for changes in participants’ circumstances which may affect their views and experiences [43]. With patients’ permission, information regarding diagnosis, disease stage, and treatments received will be obtained from patients’ medical records to decrease the research-related burden on patients. At the end of the interview, participants will be given the option to provide additional comments.

### Statistical Analysis

Preliminary analysis will involve computing descriptive statistics for all quantitative variables. For continuous variables, means, SDs, and quartiles will be estimated, while categorical variables will be summarized with counts and percentages in each category. Summaries will be performed by group and by assessment, as well as for the entire study group. Primary data analysis of the primary end point will involve comparing the frequencies of conversations about treatment options after graft loss between both groups using a 2-sided *χ*^2^ test. Secondary data analysis will include a comparison in secondary outcomes between both groups using a *χ*^2^ test. In general, test results will be described as significant if their *P* values are less than .05 without adjustments for multiple inferences. Multiple imputations will be used to deal with missing data.

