### Sample Size

The primary analysis will be performed based on the frequency of conversations about treatment options after graft loss as perceived by the patient, which is assessed in a questionnaire after the respective consultation. Based on the data from Bissonnette et al [10], we estimate that in the control group, 10%-15% of patients will have a conversation about therapy options at the end of graft function. Regarding the intervention studied herein, we estimate that this frequency can be increased to 40%-45%, which is half of the effect size achieved by Bissonnette et al [10]. Using a 2-sided *χ*^2^ test, an α error of .05, and a power of 80%, 25-49 patients per group are needed. Estimating a dropout rate of 10% per year, this increases to 31-61 patients per group. Therefore, 61 patients per group were regarded as sufficient. In order to identify 122 participating patients, local study personnel will have to screen approximately 150 potentially eligible kidney transplant recipients over a period of 6 months.

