### Randomization

Randomization will be performed using a predefined variable block randomization scheme using a web-based randomization service [18]. After screening for eligibility and assignment of the individual patient identifier, each patient-support person dyad can only be assigned once to 1 of the treatment arms. The sites will record the time of randomization.

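### Optional improvement, not an error: the primary chi-square comparison could be adjusted for pre-randomization eGFR, which every patient already has

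*Protocol article*

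**What the plan says.** All references are to the protocol article.

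- **Statistical Analysis:** "Primary data analysis of the primary end point will involve comparing the frequencies of conversations about treatment options after graft loss between both groups". The test named is the two-sided chi-square. No covariate is named. Categorical variables are summarized by counts and percentages per group, and missing data are to be handled by multiple imputation.
- **Sample Size:** the same test is used for planning. On the control rate: "we estimate that in the control group, 10%-15% of patients will have a conversation about therapy options at the end of graft function". The intervention rate is put at 40% to 45%. Then: "an α error of .05, and a power of 80%, 25-49 patients per group are needed". And: "Estimating a dropout rate of 10% per year, this increases to 31-61 patients per group". The number chosen is 61 per group.
- **Randomization:** "Randomization will be performed using a predefined variable block randomization scheme using a web-based randomization service". Allocation is 1:1 (Study Design and Setting). No stratification factor is mentioned.
- **Participants and Table 2:** eGFR below 30 mL/min/1.73 m² is an entry criterion, and the row "Serum creatinine and eGFR" is ticked at Day 0 and at every later visit.
- **Intervention Group and Details of the AI-Based DSS:** when the risk of graft loss is judged high, physicians are advised to raise it with the patient and plan replacement therapy. The AI system starts at the second visit.

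**The concern.** The conversation counted as the primary outcome is meant to follow from perceived closeness to graft loss. Among patients with eGFR below 30, baseline eGFR is the most direct routine measure of that closeness, and it is known for every patient before allocation. Neither the allocation as described nor the named test uses it.

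With about 61 per arm, the arms can differ by chance in eGFR. An unadjusted comparison leaves that variation in the noise. At stake are some power and some robustness of the result to a visible baseline imbalance. The validity of the test is not at stake.

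**Working it through.** **1. The plan's own figures.** Two-sided test, α = 0.05, power 80%, no continuity correction:

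n per group = [1.960·√(2p̄(1−p̄)) + 0.842·√(p₁(1−p₁) + p₂(1−p₂))]² / (p₂−p₁)²

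- 15% vs 40%: p̄ = 0.275; (1.2377 + 0.5102)² / 0.0625 = 48.9, so 49.
- 10% vs 45%: p̄ = 0.275; (1.2377 + 0.4889)² / 0.1225 = 24.3, so 25.
- Two years at 10% dropout leave 0.9² = 0.81: 25/0.81 = 30.9, so 31; 49/0.81 = 60.5, so 61.

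All four stated figures are reproduced.

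**2. Power of the unadjusted test at month 12.** One year of dropout leaves 61 × 0.9 = 54.9, about 55 per arm. In the least favorable planned case (15% vs 40%): z = (0.25·√55 − 1.2377)/0.6062 = 1.017, a power of about 85%. The same formula gives 80.1% at 49 and 88.1% at 61 per arm. The planned test therefore meets its target.

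**3. Power after adjustment for eGFR alone.** Trials were simulated with 55 per arm, marginal rates held at 15% and 40%, and eGFR as a standardized continuous covariate. The likelihood-ratio test for arm in a logistic model with arm and eGFR was compared with the chi-square test. The prognostic strength is an **assumption**; the article gives none.

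| Assumed log-odds per SD of eGFR | Odds ratio per SD | Chi-square power | Adjusted power |
|---|---|---|---|
| 0 to 0.3 | 1.0 to 1.35 | about 85% | 85-86% |
| 0.5 to 0.8 | 1.65 to 2.2 | about 85% | 86-89% |
| 1.2 | 3.3 | about 85% | about 91% |

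**4. Cross-check at 49 per arm** (4000 trials per row, 15% vs 40%):

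| Odds ratio per SD | Chi-square | Logistic, Wald | Standardized risk difference |
|---|---|---|---|
| 1.0 | 81.2% | 80.6% | 81.9% |
| 1.65 | 80.8% | 81.4% | 82.8% |
| 2.7 | 81.1% | 85.2% | 86.5% |
| 4.5 | 81.8% | 90.1% | 91.2% |

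The pattern is the same: almost nothing lost when eGFR is uninformative, and a useful gain only when it is fairly strong.

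**5. Type I error.** At 55 per arm the likelihood-ratio test runs slightly liberal, at about 5-6%. At 49 per arm the simulated rates are 5.1-5.2% for chi-square, 3.9-5.2% for the Wald logistic test and 5.2-6.0% for the standardized risk difference. The choice of test and variance method matters at this size.

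**6. Why conversation status at visit 1 is not a suitable covariate.**
- Table 2 has no row for it, only an undefined row named Recall. Sample Size refers to a questionnaire given after the consultation concerned.
- Recruitment Process places the first study visit after randomization, and Blinding says the trial is open. The status would be reported once the arm was known.
- The abstract describes the end point as patients who have had a conversation by 12 months. Read cumulatively, a yes at visit 1 already makes the outcome yes, and the logistic coefficient for that covariate has no finite estimate.

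**The case against.** The strongest reply is that nothing here is wrong. The chi-square test is valid, it is the test the sample size was built on, and it has its planned power. Chance imbalance is already covered by the 5% error rate. The article condenses a fuller protocol, and covariates may be settled in an analysis plan that is not shown. No prognostic strength is given, and eGFR is confined to values below 30, which may weaken it as a predictor. All of this stands, and it is why the point is optional. What remains is that the article positively names the primary test; a later adjusted primary analysis would depart from that published choice and should be fixed openly in advance.

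A reader might infer more than the article supports:

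- **That allocation is unstratified.** The article only fails to name a factor.
- **That imbalance invalidates the result.** If 40% of patients had eGFR below 20 (an assumption), the standard error of the between-arm difference would be √(2 × 0.4 × 0.6/61) = 8.9 points, and a gap of 10 points or more would occur in about 26% of randomizations (23% by exact binomial counts). This describes noise that the test already allows for.
- **That power would rise to 90-93%.** Those values need strong effects of both eGFR and prior conversation, and the second covariate is unsuitable.
- **That only a P value will be reported.** The two group percentages are planned; what the article does not name is a contrast with a confidence interval.
- **That adjustment costs nothing.** It needs prespecified methods and can be slightly liberal.

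**Conclusion.** The point holds as an optional efficiency improvement. The planned analysis is valid and adequately powered on its stated assumptions. Adjusting for pre-randomization eGFR would add roughly 0 to 6 points of power at 15% vs 40% with 55 evaluable per arm, for assumed log-odds of 0 to 1.2 per SD. It would also make the result less exposed to a chance difference in eGFR. The size of the gain is uncertain because the article gives no association between eGFR and the conversation. The downside is small: a little more analysis work, and a type I error of about 5-6% if the likelihood-ratio test is used.

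**What to change.** Before any between-arm look, specify the primary analysis as a comparison adjusted for eGFR as a continuous variable, for example a logistic model with arm and eGFR, reported as a standardized risk difference with 95% CI. Use the eligibility value, so that the covariate is clearly pre-randomization. Fix in the same text the test, the variance method and the pooling over the multiple imputations; a risk difference with its standard error pools directly by Rubin's rules. Keep the chi-square test as the supporting unadjusted analysis. Leave visit-1 conversation status out of the model.

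The cost is analysis-plan wording and modest programming. No new data, visits or patients are needed. The article reports 19 participants enrolled at 10 March 2024, so this could still be prespecified at that date. If arms have since been compared, the adjusted result should be presented as a sensitivity analysis only.

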#### Secondary End Points

As the main secondary end points, the 2 different assessment tools for SDM, the CollaboRATE mean score and the Control Preference Scale (CPS; adapted version as used in previous studies [29]), are compared between the 2 groups at 12 months after randomization. The CPS is widely used as a validated tool to assess involvement in SDM [29,30]. However, it has been suggested that CPS may be misleading in some contexts of medical decision-making since it does refer explicitly to a “decision,” whereas, CollaboRATE is a brief process-orientated measure that recognizes that study participants may not always realize that a decision has been made or have difficulties focusing on 1 decision in the context of a complex care experience [31,32]. CollaboRATE has shown discriminative validity and interrater reliability. To supplement the quantitative outcome measures, qualitative data collection in the form of interviews will be performed and analyzed. All questionnaires and interview guides will be developed with the help of a multidisciplinary research group and pilot tested with patients and support persons to optimize acceptability and feasibility. Other secondary end points are summarized in Textbox 1.

Secondary end points and time frame after which they are assessed

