**End points**
CollaboRATE mean score of all study visits from study inclusion until month 12 (values 0-9, higher values indicating better outcome)CollaboRATE mean score of all study visits from study inclusion until month 24 (values 0-9, higher values indicating better outcome)Mean Control Preferences Scale of all study visits from study inclusion until month 12 (values 1-5, higher values indicating better outcome)Mean Control Preferences Scale of all study visits from study inclusion until month 24 (values 1-5, higher values indicating better outcome)Frequency of kidney replacement therapy after graft loss at 12 monthsFrequency of kidney replacement therapy after graft loss at 24 monthsFrequency of emergency dialysis after graft loss at 12 monthsFrequency of emergency dialysis after graft loss at 24 monthsFrequency of dialysis initiation via arteriovenous-shunt after graft loss at 12 monthsFrequency of dialysis initiation via arteriovenous-shunt after graft loss at 24 monthsFrequency of dialysis initiation via permanent catheter after graft loss at 12 monthsFrequency of dialysis initiation via permanent catheter after graft loss at 24 monthsFrequency of retransplantation after graft loss at 12 monthsFrequency of retransplantation after graft loss at 24 monthsQualitative analysis of semistructured interviews after at 24 monthsQualitative analysis of physician-patient conversations after at 24 monthsFrequency of conversations about treatment options after graft loss as perceived by the patient will be compared between the 2 groups at 24 months

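### The only test named for secondary outcomes is chi-square, which does not suit the two main secondary endpoints, CollaboRATE and CPS, because both are mean scores

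*Protocol article*

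**What the plan says.** **Test.** The Statistical Analysis section of the protocol article gives a two-sided χ² test for the primary endpoint and then continues: "Secondary data analysis will include a comparison in secondary outcomes between both groups using a" χ² test. No other test is named for any secondary outcome, and no exception is made for scores. The same section sets the reporting rule, "test results will be described as significant if their" P values fall below .05, with no multiplicity adjustment.

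**Endpoints.** The Secondary End Points section gives the order of importance: "As the main secondary end points, the 2 different assessment tools for SDM, the CollaboRATE mean score and the Control Preference Scale", which "are compared between the 2 groups at 12 months after randomization". Textbox 1 then defines the scores:
- "CollaboRATE mean score of all study visits from study inclusion until month 12 (values 0-9, higher values indicating better outcome"
- "Mean Control Preferences Scale of all study visits from study inclusion until month 12 (values 1-5, higher values indicating better outcome"

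Each is repeated for month 24. The article gives no cut-point, top-score rule or other grouping for either scale.

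**Description.** For summaries, the Statistical Analysis section does separate the two kinds of variable: "For continuous variables, means, SDs, and quartiles will be estimated, while categorical variables will be summarized with counts and percentages in each category". That sentence covers description only, not the comparison between arms.

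**The concern.** A chi-square test compares how patients fall into categories. A per-patient average of a 0-9 or 1-5 score over several visits is a quantity, and the plan itself would describe it with a mean and SD. The plan therefore pairs a test for categories with endpoints that are not categories.

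CollaboRATE and CPS are the only quantitative shared decision-making (SDM) measures among the listed endpoints, and the SDM process is half of the stated objective. An analyst who follows the sentence has two routes:
- **Treat every distinct score as a category.** The test then ignores that 7 lies between 6 and 8, spreads its degrees of freedom over many thin columns and answers no question about a mean difference.
- **Group the scores.** Information is lost, and the result depends on a grouping that the article does not state. The trial is open-label and the secondary tests are unadjusted, so the grouping should be settled before the data are seen.

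**Working it through.** **1. The plan's own figure.** The only planning figure is the sample size for the primary endpoint. The pooled two-proportion formula without continuity correction is n = [1.96·√(2·p̄·q̄) + 0.8416·√(p1·q1 + p2·q2)]² / (p2 − p1)².
- 15% vs 40%: (1.2377 + 0.5102)² / 0.0625 = 48.9, so 49 per group.
- 10% vs 45%: (1.2377 + 0.4889)² / 0.1225 = 24.3, so 25 per group.
- Two years at 10% dropout: 25/0.81 = 30.9 and 49/0.81 = 60.5, so 31 and 61.

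The stated 25-49 and 31-61 per group reproduce exactly. None of this rests on the secondary scores.

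**2. How many endpoints are affected.** Textbox 1 has 17 items: 11 frequencies (chi-square fits in type), 2 qualitative analyses (no test) and 4 mean scores (two scales at two times). The mismatch concerns the 4 scores.

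**3. What the table would look like.** Table 2 places four visits up to month 12: day 0 and months 3, 6 and 12. If each visit gives one whole-number CPS value, the mean can take 4×4 + 1 = 17 values. The article does not give the number of CollaboRATE items. With k whole-number items per visit, the mean can take 4×9k + 1 values: 37 for k = 1 and 109 for k = 3.

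Take 55 per arm at month 12 (61 × 0.9 = 54.9). The simulations in step 4 show these numbers of columns actually occupied among 110 patients:

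| Score | Columns | Average expected count per cell |
|---|---|---|
| CPS | about 15 | 55/15 = 3.7 |
| CollaboRATE, k = 1 | about 22 | 55/22 = 2.5 |
| CollaboRATE, k = 3 | about 48 | 55/48 = 1.1 |

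These tables are sparse, but they are not one column per patient.

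**4. Size of the loss (all inputs assumed).** The article gives no SD, within-patient correlation, effect size or item count for either score.

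*0-9 score: visit SD 1.5, correlation 0.5, shift 0.65.*
- SD of a 4-visit mean = 1.5·√((1 + 3×0.5)/4) = 1.186, so the standardised difference is 0.65/1.186 = 0.548.
- t test: non-centrality 0.548·√(55/2) = 2.87, giving power 81%.
- Median split: the shares above the midpoint are 39.2% and 60.8%, a difference of 0.216. Then (0.216 − 1.96×0.0953)/0.0931 = 0.31, giving power 62%.
- Simulation with whole-number scores: t test about 80%, chi-square after a median split about 60%, on scores rounded to whole points about 45%, and on raw values 2% (k = 3) to 15% (k = 1).

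*1-5 score: visit SD 1.0, correlation 0.5, shift 0.5.*
- SD of the mean = 0.791, standardised difference 0.632, non-centrality 3.32, t-test power 91%.
- Simulation: t test about 90%, chi-square on raw values about 31-34%.

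**5. Range.** A separate set of simulations used 49 and 61 per group and a different variance structure (0-9 score: between-patient SD 1.5, item noise 1.2; 1-5 score: 0.7 and 0.7):

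| Score, shift | Chi-square on raw values | Welch t |
|---|---|---|
| 0-9, 0.5 | about 1% | 37-39% |
| 0-9, 1.0 | 2-5% | 87-93% |
| 1-5, 0.3 | 8-12% | 45-56% |
| 1-5, 0.5 | 31-42% | 87-94% |

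With no true effect, chi-square on raw values rejected 0.1-3% of the time instead of 5%. The t test was ahead of chi-square in every setting with a true effect.

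**The case against.** **Loose shorthand.** The sentence says neither that all secondary outcomes are tested this way nor that only this test is used. Eleven of the 17 items are frequencies, so it may have been written with those in mind. That limits the reach of the point to four items. It does not remove it, because those four include what the article calls its main secondary endpoints, and nothing else is offered for them.

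**A statistical analysis plan may settle it.** A reader might infer that the cut-point will be chosen after the data are seen. The article does not show that. An analysis plan not available here could fix a grouping in advance, and a pooled-median split can be set without looking at arm. What stands is narrower: the published plan states a test that does not fit the endpoint as defined, and a later document must either inherit that or depart from it.

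**The worst figures describe an unlikely analysis.** A reader might infer that a real difference would nearly always be missed. That holds only for chi-square on raw values. A median split still has about 60% power under the assumed inputs, which is a real loss against 80% but not a collapse.

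**A difference can still be read off.** Means and SDs will be summarised by group and by assessment, so a mean difference and its interval could be derived. That is true, but no such comparison is specified.

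**Another reading of the endpoint.** The Secondary End Points text could be taken to mean the month-12 value alone. A single whole-number CPS value would give a 2×5 table, on which chi-square can be run. It would still ignore order, and Textbox 1 defines the endpoint as a mean over visits.

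**Conclusion.** The mismatch is in the text and needs no assumption: a test for categories is the only one named, and the main secondary endpoints are mean scores with no categories defined. It covers CollaboRATE and CPS, each at 12 and 24 months.

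The size of the loss is illustrative, since every input in steps 4 and 5 of the working is assumed. The direction is firm. Categorising costs some power, and using the raw values as categories costs most of it.

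The documents do not support a stronger reading in which the trial's main result is at risk: the primary endpoint, its χ² test and the sample size are untouched. Severity: should be fixed, not a bar to the trial.

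**What to change.** In the Statistical Analysis section, split the sentence on secondary outcomes by endpoint type:
- **CollaboRATE and CPS mean scores:** a t test, a rank test or a linear model, with the mean difference and its 95% CI reported. A linear model may adjust for the visit-1 score only if that visit is not also part of the outcome mean. Textbox 1 counts visits from study inclusion, so dropping visit 1 would change the endpoint definition and must be stated as such.
- **Frequency endpoints:** keep χ², with Fisher's exact test where expected counts are small.
- **If χ² on the scores is intended:** state the categories and the reason for them before the data are examined.

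The cost is a sentence or two of wording. No new data are needed and the sample size does not change. The article reports 19 of the planned 122 participants enrolled as of March 10, 2024, so at that date the change could be made well before any comparison of the arms.
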